# The Tyrolean early vascular ageing-study (EVA-Tyrol): study protocol for a non-randomized controlled trial

**DOI:** 10.1186/s12872-020-01357-9

**Published:** 2020-02-05

## Abstract

**Background:**

According to the World Health Organization, cardiovascular diseases (CVDs) are the leading non-communicable cause of death. Awareness of the individual risk profile is crucial to implement a healthy lifestyle and prevent CVDs. Multiple studies demonstrated that atherosclerosis, the main cause of CVDs, begins early in life. Therefore, it may be necessary to start prevention programs already in childhood.

**Methods:**

The EVA-Tyrol study is a population-based non-randomized controlled trial that will prospectively enroll 2000 participants from high schools and training companies in North- and East-Tyrol (Austria) and South-Tyrol (Italy). Participants will be assigned to either an intervention (*n* = 1500) or a control (*n* = 500) group. Intervention group participants will be enrolled at the 10th school grade (mean age 15–16 years), undergo two examinations within a two-year interval, with follow-up at the 12th grade (mean ages 17–18 years). Control group participants will be enrolled at the 12th grade (mean age 17–18 years). Medical examination will include anthropometric measurements, comprehensive lifestyle and dietary questionnaires, a fasting blood sample, high-resolution ultrasound of the carotid arteries, and measurement of carotid-femoral pulse wave velocity. Active intervention will consist of (1) enhancing knowledge about CVDs, (2) individual medical counseling based on the results of the baseline examination, (3) an online health promotion tool and (4) involvement of participants in planning and implementation of health promotion projects. Effectiveness of the intervention will be assessed by comparing the proportion subjects with ideal health metrics as defined by the American Heart Association between study groups.

**Discussion:**

This study aims to improve cardiovascular health in Tyrolean adolescents by demonstrating the efficacy of a multi-layer health promotion program and may yield novel insights into the prevalence of vascular risk conditions and mechanisms of early vascular pathologies in adolescents.

**Trial registration:**

EVA-Tyrol has been retrospectively registered at clinicaltrials.gov under NCT03929692 since April 29, 2019.

## Background

According to the world health organization (WHO), 17.7 million people died from CVDs in 2015 [1, 2], with ischemic heart disease and stroke accounting for 26.6% of all deaths worldwide [3]. The Committee on Preventing the Global Epidemic of Cardiovascular Disease recommended that apart from early diagnosis and management of CVDs interventions at ‘all stages of life course’ should be performed in order to ‘promote cardiovascular health by preventing acquisition and augmentation of risk’ [4]. Awareness of the individual risk profile and subsequent modification of risk factors and risk behavior are prerequisites for effective prevention. However, it is unclear at which age best to initiate prevention.

While CVDs occur predominately in the elderly, atherosclerosis starts in early life and might even be influenced by fetal and postnatal development. According to the Barker hypothesis, early life factors such as being born preterm or small for gestational age, or impaired fetal growth or inadequate weight gain in the first years of life may predispose to CVDs later in life [5–8]. Histologic necropsy studies found coronary atherosclerotic plaques in 12% of adolescents and 28% of young adults [9]. Classical cardiovascular risk factors like smoking, physical inactivity and unhealthy diet are present not only in adults and adolescents but also in the pediatric population [10–12]. In addition, unfavorable health behaviors like sedentary lifestyle, smoking and alcohol consumption may be acquired in late childhood [13–15] and frequently persist in adulthood. Cohort studies have demonstrated the effects of risk factors on early atherosclerotic vessel wall thickening using high-resolution ultrasonography in children, adolescents and young adults [16, 17]. Conversely, a more favorable cardiovascular risk profile in childhood (as defined by the AHA) is associated with a lower aortic intima-media thickness (IMT) and a better aortic elasticity [18], and with a reduced risk of hypertension, metabolic-syndrome and elevated low-density lipoprotein cholesterol in adulthood [19]. Early correction of an unfavorable lifestyle can prevent CVDs in later life [20]. Adverse effects of obesity may be reversed by early weight reduction [20]. In Children, lifestyle and dietary counseling exhibits favorable effects on their cardiovascular risk profile without harmful side-effects [18, 21].

In summary, it is well established that cardiovascular risk factors (CVRFs) are related to early vascular ageing and early atherosclerotic wall changes in children and young adults. Promotion of a healthy lifestyle and control of CVRF. In youth presents the opportunity to reverse these changes and prevent persistence of risk conditions into adulthood. The current study will evaluate the efficacy of a defined cardiovascular health promotion program in facilitating risk factor control.

### Trial aim and objectives

The aim of EVA-Tyrol is to promote cardiovascular health in high schools/training companies by an interventional health promotion program and to acquire data on its efficacy in a cohort of Tyrolean adolescents with a mean age of 15–16 years.

The primary objectives of EVA-Tyrol are:
To assess health in the Tyrolean youthTo survey the effect of a multi-layer health promotion program in this age groupTo study the effects of neonatal and childhood weight gain on CVRF in youthTo assess the effects of being born preterm or small for gestational age on vascular health in youthTo determine the effects of CVRF on vascular health in youthTo explore the effects of lifestyle on vascular health in youthTo establish a serum biobank

## Methods and design

### Study design

The EVA-study is a non-randomized controlled trial. Two thousand participants will be recruited from high schools and training companies spread over North- and East-Tyrol (Austria) and South-Tyrol (Italy). Study participants will be assigned to i) health intervention group (*n* = 1500) or ii) control group (*n* = 500). For participants included in the intervention group two examinations will be scheduled within a two-year interval between the examinations. Participants will be in the 10th grade (mean age, 15–16 years) at the baseline and in the 12th grade (mean age, 17–18 years) at the follow-up examination. Between the examinations the health intervention program will be offered.

Five hundred participants with a mean age of 17–18 years without participation in a health promotion program will serve as a control group. The prevalence of AHA health metrics in the intervention group will be compared to the prevalence in the control group (Fig. 1).

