#### Inclusion criteria

Participants in the 10th to 12th grade (mean ages 15–16 at baseline for the intervention group and 17–18 years for the control group) will be enrolled. Informed consent by the participant and, for participants younger than 18 years, their legal representative will be obtained. Consent for inclusion of data from the “mother-child booklet” additional maternal informed consent will be obtained.

Schools and training companies will be randomly assigned to either the intervention or the control group. The examination of the intervention group will start first. Schools will be assigned to either group according to their available schedule. The exact number of participating schools/training companies will depend on the number of participants per school/company.

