#### Exclusion criteria

None; previous or concurrent diseases are not an exclusion criterion.

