### Data acquisition

The study will take place at the schools’ or training companies’ sites. An overview of the trial procedures is depicted in Fig. 2. Data will be collected by a paper case report form (CRF) and include a self-administered and assisted questionnaire, a structured interview and a series of examinations (blood sampling, high-resolution ultrasound of the carotid arteries, tonometric measurement of carotid-femoral pulse-wave velocity, blood-pressure measurement and anthropometry). Data acquisition will be done by medical doctors assisted by medical students.

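### Pupils who join a site after 10th grade, or repeat a year on the way to 12th, can appear only among controls, so the primary comparison mixes school trajectory with the programme effect

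*Protocol article*

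**What the plan says.** **Intervention arm.** The Study design section of the protocol article fixes both time points: "Participants will be in the 10th grade (mean age, 15–16 years) at the baseline and in the 12th grade" at the follow-up examination. The Abstract agrees: "Intervention group participants will be enrolled at the 10th school grade (mean age 15–16 years), undergo two examinations within a two-year interval". Under Data acquisition, "The study will take place at the schools’ or training companies’ sites".

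**Control arm.** The Abstract states: "Control group participants will be enrolled at the 12th grade (mean age 17–18 years"). Study design adds: "Five hundred participants with a mean age of 17–18 years without participation in a health promotion program will serve as a control group". The Inclusion criteria section sets entry by grade and consent. On exclusions the article says: "None; previous or concurrent diseases are not an exclusion criterion". No condition concerns where a control was two years earlier.

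**Comparison.** Under Outcome measures and statistical analysis, the proportion in the ideal range on each of the seven metrics is compared between arms by Chi-squared test. Logistic regression is mentioned without named covariates. The sample size statement gives 95% power with 2000 participants split 3:1. The detectable difference runs from 3 points at a control proportion of 96% to 10 points at 50%.

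**The concern.** Both arms are compared in 12th grade, but they reach it under different rules. An intervention pupil must have been enrolled at a participating site in 10th grade and be in 12th grade two years later. A control need only be in 12th grade on the day. Two kinds of pupil are therefore admitted on one side only: those who joined the school or company after 10th grade, and those who repeated a year after 10th grade.

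Changing school and repeating a year may well go with smoking, diet, activity or weight, which are themselves primary metrics. If so, part of the between-group difference reflects school trajectory. A Chi-squared test cannot separate the two. Controls have no 10th-grade examination, and no topic listed in Table 1 is school or training history.

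**Working it through.** **1. Who can be compared, by the article's own rules** (follow-up in 12th grade at the site)

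| Pupil | Intervention | Control |
|---|---|---|
| In 10th grade at the site, promoted, still there | yes | yes |
| Repeated before 10th grade, or repeating 10th grade at enrolment | yes | yes |
| Joined the site after 10th grade | no | yes |
| Repeated a year after the 10th-grade examination | no (in 11th grade two years later) | yes |
| Left before 12th grade | no | no |

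The arms differ in the third and fourth rows. A pupil who moves from one intervention site to another is left aside.

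**2. The plan's own figures.** Inputs: 500 controls, 1500 intervention pupils, independent pupils, two-sided alpha 5% (an assumption, as the article states none).
- 96% against 99%: power 96.7%.
- 50% against 60%: power 97.4%.

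The stated 95% holds at both ends. The power statement is not in question and serves only as a yardstick.

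**3. Illustrative shift in the control proportion.** The documents give no rates, so f and g are assumptions: f is the share of controls who are newcomers or repeaters, and g is how far their ideal proportion lies below that of other pupils. With no programme effect, shift = f × g:
- central: 0.10 × 15 = 1.5 points
- low: 0.05 × 10 = 0.5 points
- high: 0.20 × 20 = 4.0 points

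**4. Effect on the test at a proportion near 50%.** SE = √(0.25/500 + 0.25/1500) = √0.000667 = 0.0258, or 2.6 points. The two-sided rejection rate is P(|Z + shift/SE| > 1.96):
- shift 0.5: 0.5/2.58 = 0.19, rate about 5.4%
- shift 1.5: 1.5/2.58 = 0.58, rate about 9%
- shift 4.0: 4.0/2.58 = 1.55, rate about 34%

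**5. Yardstick at the same proportion.** At 50% the stated detectable difference is 10 points. The central shift is 1.5/10 = 15% of it and the extreme is 40%.

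These gaps cannot hold for every metric. The article puts ideal diet below 5%, where a deficit of 10 points or more is impossible.

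**The case against.** The article openly declares the design: "The EVA-study is a non-randomized controlled trial", with controls examined once. No figure in it is wrong. It may also leave analysis populations and covariates to a fuller document, and the item wording of the questionnaire is not shown. Age would partly mark repeaters, and logistic regression is planned. Restricting to stayers narrows the conclusion and takes pupils from the smaller arm.

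Much of this stands. It limits the point to an avoidable selection difference, and it means nobody can say that the collected data could never address it. It does not remove the mismatch, which lies in entry rules that the article states itself. The non-randomized label warns of confounding in general but does not deal with this source. Nor would assigning whole schools by chance, since the rule on who may enter from a school would still differ by arm.

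A reader might infer that early leavers also unbalance the arms, even with perfect follow-up. The article does not support that. It places the compared examination in 12th grade and on site, so leavers are absent from both arms. They would matter only if intervention leavers were traced or imputed, which the article does not propose.

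A reader might also set the 1.5-point shift against the 3-point difference. That figure belongs to a control proportion of 96%, whereas the error rates above are for 50%.

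**Conclusion.** The concern holds in a limited form. As written, later arrivals and pupils who repeated a year between 10th and 12th grade can enter the primary comparison only as controls, and the unadjusted test does not separate their influence from the programme's. Size and direction cannot be derived from the documents. If turnover is low, or if these pupils resemble the rest, the effect is negligible. Under the assumptions shown, it is small beside the 10-point difference but large enough to disturb the error rate for a metric near 50%. The 34% figure needs both extreme assumptions together. All error rates treat pupils as independent. This is a cheap improvement to the plan, not a flaw that invalidates it.

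**What to change.** Add one item to the control questionnaire: was the pupil in 10th grade at this school or company two years earlier? Prespecify the between-group comparison in pupils who meet the same condition in both arms: in 10th grade at that site two years before, and in 12th grade there at the compared examination. Report it alongside the comparison with all examined controls. Which of the two is labelled primary matters less than having both fixed in advance. If control examinations are already complete, enrolment records at the school or company might supply the same fact.

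The cost is one question and one population definition, some loss of controls, and a conclusion for that comparison limited to pupils who stay in their school or company. Under the assumed 10% (range 5–20%), 450 controls remain (range 475–400). The SE near 50% then becomes √(0.25/450 + 0.25/1500) = 2.7 points, or 2.8 points with 400 controls, against 2.6 with all 500.

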**Fig. 1 Fig1:**
[figure not shown]
Schematic illustration of study design

In addition to health metrics, EVA-Tyrol will evaluate further components and determinants of cardiovascular health of Tyrolean adolescents. In addition, we will collect information on the first 6 years of life including pre-, peri- and postnatal data prospectively documented in the mother-child booklet, the official Austrian pregnancy and early childhood medical record book.

### Participants

#### Recruitment

The local education authority (Landesschulrat for Tyrol) will brief all Tyrolean high schools about the project. Subsequently, the schools will be able to apply for study-inclusion. In order to ensure a homogenous regional and social distribution, principals of selected schools will be actively encouraged to participate. Schools and training companies will not receive financial compensation for participation. The two study centers will be Innsbruck (Austria) for North and East Tyrol and Bruneck (Italy) for South Tyrol. Moreover, Tyrolean training companies will be invited to participate. For participating schools and companies a project presentation on the background of CVD and concept of CVRF will be offered. Pupils and trainees will be briefed about the study procedure. In addition, a video summarizing study aims and procedures will be shown.

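### The allocation rule is stated inconsistently (random, by schedule, non-randomized), and under the schedule rule nothing shown keeps schools' entry routes balanced between the groups

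*Protocol article*

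**What the plan says.** **Entry (Recruitment).** All Tyrolean high schools are briefed by the education authority. "Subsequently, the schools will be able to apply for study-inclusion". A second route serves to even out the regional and social mix: "principals of selected schools will be actively encouraged to participate". Companies have a third: "Moreover, Tyrolean training companies will be invited to participate". The section gives no timing for encouragement relative to application.

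**Allocation (Inclusion criteria).** Three consecutive sentences bear on it:
- The first makes allocation random for both kinds of site: "Schools and training companies will be randomly assigned to either the intervention or the control group".
- The next gives the order of work: "The examination of the intervention group will start first".
- The last makes the calendar decide for schools: "Schools will be assigned to either group according to their available schedule".

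**Design label (Study design; the title says the same).** "The EVA-study is a non-randomized controlled trial".

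**Comparison (Abstract, Study design, Outcome measures and statistical analysis).** About 1500 intervention participants are seen in the 10th and 12th grades. About 500 controls are enrolled only in the 12th grade. The primary outcome, the between-group difference in the proportion ideal on each of the seven health metrics, is tested by chi-squared. Logistic regression is named for multivariate analysis, without covariates.

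**The concern.** A site cannot be placed both at random and by its calendar, and neither a random rule nor a mixed one fits a non-randomized label easily. The choice matters because it decides whether differences between schools that existed before the programme are left to chance or can be linked to group.

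Under a schedule rule, availability determines group. Availability may be related to how a site came into the study: a school that applied after the briefing and one whose principal was approached may differ in readiness, and also in pupils' health habits. The plan itself uses encouragement to even out region and social mix, so it does not expect applicants alone to supply that mix.

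Nothing shown records entry route or balances it between groups. Evening out region and social background over the whole sample does not balance route between the two groups. At stake is the efficacy claim: a route-related difference would appear in the 12th-grade comparison as an effect of the programme, or would mask one.

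**Working it through.** **1. The allocation statements side by side**

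| Place | Rule | Applies to |
|---|---|---|
| Inclusion criteria, first statement | random | schools and training companies |
| Inclusion criteria, later statement | available schedule | schools |
| Title, Study design | non-randomized | the trial |

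If the first is the rule used, entry route can differ between groups only by chance. If the second is used, route and group can be associated. The document does not say which was applied.

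**2. Can the planned comparison detect or remove a route difference?**
- The primary test is a chi-squared test without adjustment, so it cannot remove one.
- Controls have no 10th-grade examination, so no earlier between-group comparison could reveal one.
- The secondary outcome is change within the intervention group. It does not depend on differences between groups, but it has no concurrent control for age and cannot repair the primary comparison.

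**3. The plan's own figures, for scale**

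With 500 against 1500 and two-sided 5% (assumed, since the power statement gives no alpha), power is 97.4% for 50% against 60%, and 96.7% for 96% against 99%. The stated 95% is met at both ends for an increase. The power figure is not in dispute here; the 10-point difference at 50% serves only as a yardstick.

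**4. Illustration of size (inputs assumed, not from the document)**

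Spurious difference = (difference between groups in the share from self-applied schools) × (difference in the ideal proportion between routes).
- Low: 0.30 × 5 points = 1.5 points.
- High: 0.50 × 10 points = 5 points.

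Standard error at about 50% ideal, treating pupils as independent: √[0.25 × (1/1500 + 1/500)] = 2.58 points.
- Low: z = 1.5/2.58 = 0.58, so the nominal two-sided 5% test rejects about 9% of the time.
- High: z = 5/2.58 = 1.94, so it rejects about 49% of the time.

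Both are with no programme effect. Five points is half of the 10-point difference used in the power statement.

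A wider set of assumptions (imbalance 0.2 to 0.6, gap between routes 5 to 15 points) gives spurious differences of 0.2 × 5 = 1 point to 0.6 × 15 = 9 points. The chance of a significant result favouring the programme is then about 6% at 1 point, 12% at 2, 34% at 4, 65% at 6 and 94% at 9, against 2.5% with no imbalance. The result follows the inputs closely, so it shows what could happen and does not estimate what did.

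**The case against.** A reader might infer that self-motivated schools come forward first, fill the intervention group, and so bias the result towards the programme. The document does not support that chain. The sentence on timing concerns the order of examinations, and the next concerns calendar availability; neither mentions order of application. Nothing says that encouraged schools come later. Both groups draw on the same routes, and control schools also agreed to join a cardiovascular health study.

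The direction is open too. A school might apply because it sees a health problem, and a principal's decision is a weak proxy for pupils' cholesterol or body-mass index. The illustration covers only a metric near 50%, whereas the protocol quotes prevalences from under 5% to over 80%. Encouragement is not a fault in itself, since it widens the sample beyond volunteers. If random assignment was the rule used, the mechanism fails. The covariates for the logistic regression may be listed in a fuller document.

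All of this stands, and it limits the point to a possibility under one of the stated rules. It does not remove the contradiction within a single paragraph. Nor can the random-assignment sentence be relied on as protection while the schedule rule and the non-randomized label stand beside it. Allocation is a design matter that this article fixes itself, not a detail left to an analysis plan.

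**Conclusion.** The point holds in a limited form. It is certain from the text that the allocation statements conflict and must be reconciled. It is conditional on the schedule rule that group may be associated with entry route, since nothing shown prevents it. In that case the unadjusted comparison, with no 10th-grade control examination, could not separate a prior school difference from the programme effect.

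Neither the sign nor the size of such a difference can be derived from the document. The 1.5 to 5 points, and the 9% to 49% rejection, rest on an assumed 30 to 50 point imbalance in route, an assumed 5 to 10 point gap between routes, about 50% ideal, and independent pupils. That early or self-motivated schools were in fact placed in the intervention group is not established. The change is worth making because it is cheap, reduces possible bias under the schedule rule, and does no harm under random assignment.

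**What to change.** 1. State the one allocation rule actually used for schools and for companies, and bring the Inclusion criteria section, Study design and title into line with it.
2. Record for each site the entry route, in three categories (applied, encouraged, invited company), and the entry date. Fix in advance how a school that was encouraged and then applied is coded.
3. While slots remain, assign within route at about 3:1, so that each route appears in both groups in similar proportion.
4. Include route as a covariate in the logistic regression for the between-group comparison, and report that adjusted result beside the chi-squared test.
5. Add a sensitivity comparison restricted to self-applied schools.

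If assignment is already complete, step 3 falls away; route can be taken from recruitment records for steps 4 and 5, and the rule that was used should still be stated.

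**Cost.** Two items per site (route and date), a scheduling rule and one covariate. Booking of dates becomes slightly less free. The restricted comparison loses precision because the control group of 500 shrinks further. For example, if half of each group were self-applied (an assumption), the standard error at 50% would be √[0.25 × (1/750 + 1/250)] = 3.65 points instead of 2.58. Adjustment also helps only where both groups contain each route, which is the reason to balance at assignment while that is still possible.
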